#### Descriptives

Descriptive analysis will be performed to compare the baseline characteristics of both groups.

• Continuous data (age, BMI, length, and so on): Averages with standard deviation (parametric data) or medians with percentiles (non-parametric data) will be calculated for both groups.

• Categorical data (TASC type, co-morbidities, and so on): Frequencies will be calculated for both groups.

Distribution of Rutherford categories during baseline and follow-up will be given as percentages per category. No statistical analysis will be performed.

#### Comparative statistics

The primary and secondary endpoints as mentioned in ’Endpoints/parameters’ will be compared using statistical methods.

#### Actuarial analysis

Absence of binary restenosis rate and reocclusion rate will be calculated with actuarial (life-table) analysis and will be expressed as a percentage with a standard error and 95% CIs. Logrank tests will be used to determine if differences between the estimates are significant. For these endpoints, we will also calculate a combined endpoint with survival, for example, binary restenosis-free survival etc. Based on the literature, we expect that mortality will be negligible and will not influence the results, and these separate analyses will be performed to check this assumption.

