## Methods/Design

### Objectives

#### Primary objective

• To assess the absence of binary restenosis rate of advanced atherosclerotic lesions of the common iliac artery with a balloon-expandable PTFE-covered stent (Advanta V12, Atrium Medical Inc., Hudson, NH, USA), when compared to selected balloon-expandable uncovered stents, in a 2-year follow-up period.

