### Study Design

A prospective, randomized, controlled, double-blind, multi-center trial with a follow-up period of 2 years.

Centers currently participating are:

• Maasstad Hospital, Rotterdam, The Netherlands

• Sint Antonius Hospital, Nieuwegein, The Netherlands

More centers may be added during the course of the trial.

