#### Primary endpoint

• Absence of binary restenosis rate. Defined as the percentage of limbs with absence of hemodynamically significant obstruction in the target-lesion after endovascular treatment.

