#### 6, 12 and 24 months postoperative

At 6, 12 and 24 months, ABI and treadmill test will be performed, as well as a DUS, and patients will be asked to fill in the RAND-36 and WIQ. If DUS shows a stenosis, defined as a peak systolic velocity rate of ≥2.4, or is inconclusive, CT-A, MR-A or DSA will be performed. If an in-stent stenosis or occlusion is identified, this will be documented and treated within 1 month. Table 3 summarizes the study procedures at different moments.

**Table 3 T3:** Study procedures

	**Pre-ope-rative**	**Per-ope-rative**	**1 month**	**6 months**	**12 months**	**24 months**	**In case of restenosis**
DUS	X			X	X	X	X
ABI (with or with-out treadmill test)	X		X	X	X	X	X
DSA		X					X
WIQ/RAND-36	X		X	X	X	X	

DUS = Duplex ultrasonography, ABI = Ankle-brachial index, DSA = Digital subtraction angiography, WIQ = Walking Impairment Questionnaire, RAND-36 = RAND 36-Item Health Survey.

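### The planned life table misstates the 2-year restenosis-free percentage because the 24-month scan both detects late restenosis and ends follow-up

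*Protocol article*

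**What the plan says.** All references are to the protocol article.

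- **Endpoint** (Primary endpoint): "Defined as the percentage of limbs with absence of hemodynamically significant obstruction in the target-lesion after endovascular treatment". The Primary objective sets the comparison "when compared to selected balloon-expandable uncovered stents, in a 2-year follow-up period", and the Data safety monitoring board section says that the main outcomes are scored at 2 years.
- **Detection** (6, 12 and 24 months postoperative): "At 6, 12 and 24 months, ABI and treadmill test will be performed, as well as a DUS". If the ultrasound is positive "or is inconclusive, CT-A, MR-A or DSA will be performed". Under Unplanned visits, an ultrasound is also mandatory for patients who present with symptoms between visits.
- **End of follow-up** (Study Design): "multi-center trial with a follow-up period of 2 years", the same time as the last ultrasound.
- **Estimator and test** (Actuarial analysis): one sentence covers the primary endpoint and reocclusion together and reads "reocclusion rate will be calculated with actuarial (life-table) analysis and will be expressed as a percentage with a standard error and 95% CIs". For the comparison of arms, the section then says: "Logrank tests will be used to determine if differences between the estimates are significant".

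**The concern.** An actuarial table assumes that patients who leave during an interval were, on average, observed for half of it, so it subtracts half of them from the number at risk. That suits withdrawals spread over an interval. Here almost everyone who leaves does so at the 24-month scan, after being observed for the whole interval and found clear, and silent restenoses from the preceding 12 months are dated at that same visit. If the last interval includes the scan, the risk set is nearly halved while every event is counted, so the percentage is too low. If the table stops before the scan, those events are lost and the percentage is too high.

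At stake is the reported primary result: the 2-year percentage in each arm, its standard error and confidence interval, and the difference between arms.

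**Working it through.** **1. The plan's own figure.** Sample size calculation gives 90% v 72% at 2 years, alpha 0.05, beta 0.2 and 79 per group.
- HR = ln(0.90)/ln(0.72) = 0.321.
- Freedman's formula, two-sided: (1.960 + 0.842)² × [(1 + 0.321)/(1 − 0.321)]² = 29.7, so 30 events.
- The average event probability is (0.10 + 0.28)/2 = 0.19, and 30/0.19/2 = 78.9, so 79 per group.

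The stated figure reproduces.

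**2. Worked life table.** Inputs from the document: 72% and 90%, n = 79, scans at 6, 12 and 24 months. Assumed: constant hazard, no loss, every visit on time, no symptom-detected events. Restenosis is dated at the scan that finds it, and clear patients are censored at their 24-month scan.

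| | Uncovered | Covered |
|---|---|---|
| Restenosis-free at 12 months (√0.72, √0.90) | 84.9% | 94.9% |
| At risk after month 12 | 67.0 | 74.9 |
| Found at the 24-month scan | 10.2 | 3.8 |
| Clear at the 24-month scan | 56.9 | 71.1 |
| Exposure = at risk − ½ × clear | 38.6 | 39.4 |
| Interval risk = found/exposure | 0.263 | 0.098 |
| Life table, last interval holds the scan | 62.5% | 85.6% |
| Life table stopped before the scan | 84.9% | 94.9% |
| True value | 72% | 90% |

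The difference between arms is 85.6 − 62.5 = 23 points or 94.9 − 84.9 = 10 points, against a true 18.

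**3. Standard error, uncovered arm.** Greenwood's sum is (1 − 0.849)/(79 × 0.849) + 0.263/(38.6 × 0.737) = 0.0023 + 0.0093 = 0.0115. The SE is 0.625 × √0.0115 = 6.7 points. With all 79 patients fully observed it is √(0.72 × 0.28/79) = 5.1 points.

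**4. Scatter in visit dates.** Simulations with 87 per arm; the article gives no scatter, so these values are assumptions.
- SD 1 month, no symptom-detected events: 56.1% v 82.6% if the table includes a 24-30 month interval, and 77.2% v 92.0% if it stops at 24 months.
- All visits 0 to 1 month early: 63% v 86%.
- All visits 0 to 1 month late: 84% v 95%.

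**5. Symptomatic detection.** Assume half of restenoses are found at onset; the article gives no share.
- On-time visits, table stopped before the 24-month scan: only half of the month 12-24 events are missed, so 72 + (84.9 − 72)/2 = 78% and 90 + (94.9 − 90)/2 = 92%.
- On-time visits, scan in its own interval (uncovered arm): at risk 67.0 − 5.1 = 62.0, found 5.1, exposure 62.0 − 28.4 = 33.5, giving 0.849 × (62.0/67.0) × (1 − 5.1/33.5) = 67%.
- On-time visits, one interval covering month 12 up to and including the scan: the counts are those in the table above, so 62.5% and 85.6% are unchanged.
- Simulation, SD 1 month: 61.5% v 85.8% (to 30 months) and 74.0% v 90.5% (to 24 months).

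**6. After the fix.** With all 24-month-visit scans coded to month 24 and events counted before censoring, the last step uses the full risk set: 0.849 × (1 − 10.2/67.0) = 72.0%, and 90.0% in the covered arm. Simulated means are 71.7-72.2% and 89.7-90.2%, with or without 10% loss.

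**The case against.** The best defence is that the article states only a life table and a log-rank test. Interval boundaries, visit windows, event dating and the handling of completers may be set in a full protocol or analysis plan, and their absence here is not a fault. Scans are indexed by visit and outcomes scored at 2 years, which leans towards visit-based counting. That is fair as far as it goes, and it is why the size of the error cannot be fixed from the article. It does not remove the problem. Estimator, scan schedule and end of follow-up are all stated, and in the on-time worked example neither placement of the last boundary returns 72% and 90%.

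Symptomatic detection also counts in the plan's favour. With half found at onset, symmetric scatter and a table stopped at 24 months, the errors largely cancel (74.0% v 90.5%). That depends on appointment timing and an unknown symptomatic share, not on the method.

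Three stronger readings are tempting but not supported:
- A reader might infer errors as large as 39% v 73%. Those values come from a Kaplan-Meier curve with every patient scanned early; the plan names a life table.
- A reader might infer that the primary test or the sample size fails. Both arms share one schedule, so the log-rank comparison is not materially affected, and 79 per group reproduces. In simulation, grouping to nominal visits left power unchanged (84.7% v 84.4%).
- A reader might blame appointment scatter alone and think coding to nominal visits cures it. The half-withdrawal rule biases the table even with perfect timing.

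**Conclusion.** The concern holds for estimation, not for testing. With the protocol's rates, on-time visits and silent restenosis only, the life table is too low by 9.5 points (uncovered) and 4.4 points (covered), or too high by 12.9 and 4.9 points, depending only on which side of the last boundary the 24-month scans fall. The standard errors and confidence intervals are wrong with it.

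This rests on a constant hazard, no loss and detection only at scheduled scans. With half of restenoses found through symptoms, the range is about 62-78% v 86-92%, depending on boundaries and visit timing. Restenoses found by the 6- or 12-month scan do not contribute to the error. It is worth correcting because the endpoint is itself defined as a percentage.

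**What to change.** In Actuarial analysis, replace the life-table percentage with one of:
- a product-limit estimate on nominal visit times, with all 24-month-visit scans coded to month 24, events counted before end-of-study censoring, and no half-withdrawal adjustment for completers; or
- an interval-censored (Turnbull) estimate, with restenosis placed between the last clear and the first positive scan.

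Censor deaths and losses at the last scan rather than the last contact. Keep the log-rank test, run on the grouped times. A standard life table on nominal visits is not adequate: it still gives about 63% v 86%.

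The cost is a change of analysis wording and a little more programming. It needs no new data and no change to the sample size.

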#### Sample size calculation

Based on the available literature [53,54], we expect a 2-year absence of binary restenosis rate of 90% in the PTFE-covered stent group, and a 2-year absence of binary restenosis rate of 72% in the uncovered stent group. Based on the log rank test for equality of survival curves, with an alpha error level of 0.05 and a beta error level of 0.2, 79 patients per group will be necessary. We anticipate a loss to follow-up of less than 10%, so we will include 87 patients per group, for a total of 174 patients. This calculation was performed using nQuery Advisor (Statistical Solutions Ltd., Farmer’s Cross, Ireland). The combined participating centers perform over 200 endovascular procedures for advanced iliac PAOD annually. With an estimated participation rate of 75%, estimated inclusion time is 2 years.

No sample size calculation was performed for the subgroups as there is no data available on freedom of binary restenosis rates for these groups, and therefore no well-founded calculation can be made.

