### Randomization, blinding and treatment allocation

All symptomatic patients in whom a hemodynamically significant lesion of the CIA is suspected will be included. This is assessed using DUS and either CT-angiography or MR-angiography. A hemodynamically significant lesion is suspected if DUS shows a peak systolic velocity ratio of ≥2.4 and/or CT-angiography or MR-angiography shows a diameter reduction of ≥50%. Any suspected significant lesion is initially included, and informed consent obtained, even if pre-operative imaging shows a stenosis with a length of less than 3 cm. After the pre-intervention DSA and intra-arterial systolic blood pressure gradient measurement have been performed, the treating physician will make the final decision if the patient meets the inclusion criteria. If there is a stenosis with a length of more than 3 cm, or an occlusion, the patient will be randomized. All patients with stenoses with a length of less than 3 cm will be excluded, but they will be registered, and informed consent will have been obtained to store their data (Figure 2). Randomization will be performed using an online registration and randomization program (Trans European Network for Clinical Trial Services (TENALEA), http://tenalea.net). Unstratified randomization will be used, with a minimization algorithm based on occlusion vs stenosis, and endovascular vs hybrid procedures. If a patient has bilateral iliac lesions that are eligible, the symptomatic limb will be included. In case both limbs are symptomatic, the leg with the lowest ABI will be included. Both legs will receive the same treatment. The patient will be allocated to either the Advanta V12 PTFE-covered stent, or to an uncovered balloon-expandable stent. Patients will be blinded for the treatment they receive. When patients are under local or regional anesthesia, a sterile operating theatre napkin will be placed in such a manner that the patient cannot see the procedure and the stent in particular. The physician will make sure not to mention the type of stent prior, during or after the procedure. The physician performing the procedure will not be blinded, as this is not possible practically. The type of stent used will not be documented in the patient’s medical record. Post-operative ABI’s, DUS and scoring of Rutherford classification will be performed by vascular technicians who are blinded for the type of stent used. Therefore, this is a double-blind study.

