### Statistical analysis

Statistical analysis will be performed for the complete study population, as well as subgroup analysis for patients with IC vs CLI, occlusions vs stenoses, and endovascular vs hybrid procedures.

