#### Univariate analysis

Univariate analysis will be performed to assess differences in the other aforementioned primary and secondary endpoints.

Continuous data: Averages with standard deviation (parametric data) or medians with percentiles (non-parametric data) will be calculated. Differences between both groups will be tested using a Student’s *t*-test (parametric data) or a Mann–Whitney *U*-test (non-parametric data). Differences with a *P*-value <0.05 will be considered statistically significant. The following endpoints will be assessed:

Post-intervention COT and ACT;

Mean ABI.

Categorical data: Frequencies will be calculated and difference between both groups will be tested using Chi-squared test. Differences with a *P*-value <0.05 will be considered statistically significant. The following secondary endpoints will be assessed:

• Target lesion revascularization rate and target extremity revascularization rate;

• Procedural, technical and device success rate;

Mortality rate, complication rate, amputation rate;

• Rate of device-specific problems.

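### The primary log-rank test does not use the two minimisation factors; if they predict restenosis it is mildly conservative and gives up a little power, but it stays valid

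*Protocol article*

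**What the plan says.** All references are to the protocol article.

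- **Allocation** (Randomization, blinding and treatment allocation): "Unstratified randomization will be used, with a minimization algorithm based on occlusion vs stenosis, and endovascular vs hybrid procedures".
- **Primary test** (Actuarial analysis): the restenosis and reocclusion endpoints are estimated by life table, with standard errors and 95% confidence intervals, and "Logrank tests will be used to determine if differences between the estimates are significant". No stratification or covariate is named.
- **Remaining endpoints** (Univariate analysis): "Univariate analysis will be performed to assess differences in the other aforementioned primary and secondary endpoints", by t, Mann–Whitney or chi-squared tests.
- **Where the factors reappear** (Statistical analysis): only in the "subgroup analysis for patients with IC vs CLI, occlusions vs stenoses, and endovascular vs hybrid procedures". The first of these three, claudication versus critical ischaemia, is not a minimisation factor.
- **Sample size** (Sample size calculation): also built on a log-rank test with no strata: "with an alpha error level of 0.05 and a beta error level of 0.2, 79 patients per group will be necessary".

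**The concern.** Minimisation removes most of the chance imbalance between arms on the factors it uses. If those factors predict restenosis, the treatment comparison varies less from trial to trial than it would under simple randomisation. A plain log-rank test does not take credit for this. Its variance still allows for between-arm differences that the design has largely prevented, so its true error rate falls below the nominal 5% and it has less power than a test that conditions on the factors.

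The trial is small in events. At the planned rates, 87 × 0.28 + 87 × 0.10 = 33 restenoses are expected among 174 patients. Precision that the design has already secured is worth keeping, above all if the true effect is smaller than the one assumed.

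**Working it through.** **Inputs from the protocol article.** For the covered stent, "we expect a 2-year absence of binary restenosis rate of 90% in the PTFE-covered stent group"; the matching assumption for uncovered stents is 72%. Alpha is 0.05 (sidedness not stated), power 80%, with 79 per group, raised to 87 per group (174 in total) for losses below 10%.

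**Step 1: reproduce the stated sample size.**

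- HR = ln(0.90)/ln(0.72) = 0.321.
- Freedman, two-sided 0.05: events = (1.960 + 0.842)² × [(1 + 0.321)/(1 − 0.321)]² = 29.7.
- Per arm: 29.7/(2 − 0.90 − 0.72) = 29.7/0.38 = 78.1, rounded up to 79, as stated.
- 79 × 1.1 = 86.9, that is 87 per group, as stated.

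The trial was therefore sized for the plain, two-sided log-rank test.

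**Step 2: simulate both tests under minimisation.** The article gives no prognostic strength or prevalence for either factor, so these are assumptions: 50% occlusions, 30% hybrid procedures, and a range of hazard ratios. Each trial has 158 evaluable patients, minimisation on the two factors with a biased coin of 0.8, exponential times censored at 2 years, and marginal 2-year rates held at 72% and 90% (or 72% in both arms under the null). The stratified test uses the four factor cells. There were 10,000 trials per setting; Monte Carlo standard error is about 0.2 points for type I error and 0.4 for power.

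| Occlusion HR / hybrid HR | Type I error, plain | Type I error, stratified | Power, plain | Power, stratified | Gain (points) |
|---|---|---|---|---|---|
| 1 / 1 | 4.84% | 4.68% | 83.51% | 83.24% | −0.27 |
| 1.5 / 1.5 | 4.67% | 5.00% | 84.19% | 84.34% | 0.15 |
| 2 / 2 | 4.38% | 5.13% | 84.98% | 85.90% | 0.92 |
| 3 / 2 | 3.83% | 4.83% | 85.44% | 87.09% | 1.65 |
| 4 / 3 | 2.86% | 5.06% | 85.61% | 88.70% | 3.09 |

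Deterministic minimisation gives the same pattern, with gains of 0.52 at 2/2, 1.63 at 3/2 and 3.47 at 4/3. A separate set of 3,000 trials, with exact balance within cells, 35% hybrid procedures and restenosis detected only at the 6-, 12- and 24-month scans, gave type I error of 4.0% against 5.1% and power of 82.5% against 84.6% at 3/2.

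**Step 3: a smaller treatment effect.** Take HR 0.45 in place of 0.32. Without prognostic factors this means 0.72^0.45 = 86% free of restenosis with the covered stent.

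- At 3/2, the scan-based simulation gives 56.8% against 61.0% (4.2 points), and the minimisation set-up of step 2 gives 58.3% against 61.6% (3.3 points).
- At 4/2, the step 2 set-up gives 56.1% against 61.1% (5.0 points).
- At 1/1, stratifying costs 61.2% − 60.3% = 0.9 points.

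**The case against.** **The premise is not documented.** The article gives no reason for choosing these two factors, and its sample size section says that restenosis data for the subgroups do not exist. This stands. The loss is conditional: at 1/1 there is none, and at 1.5/1.5 it is within simulation error. A reader might infer that the factors were picked because they are known to be prognostic; the text does not say so.

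**Nothing planned is lost.** A reader might infer that the trial is underpowered or its test invalid. Neither follows. The sample size was computed for this very test, which keeps 83.5% to 85.6% power in the table, above the planned 80%. The error is on the safe side, so a significant result can be trusted. The shortfall is only relative to a better test.

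**Stratification may be left to an analysis plan.** The plan is not shown and might add strata. But the article is not silent on the analysis: it names the test for each endpoint and gives the factors a different role, as subgroups. Naming the stratified test improves a stated choice.

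**Two further readings go too far.** One is that the hazard ratio would be biased toward 1. No hazard ratio is planned; the actuarial section reports life-table percentages and a log-rank test. A gap between unadjusted and adjusted hazard ratios also reflects two different estimands (non-collapsibility), which is not an error. The other is that the t-test and chi-squared endpoints suffer as well. The simulations cover only the log-rank test, so no loss has been shown there.

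**Conclusion.** The mismatch between allocation and analysis is real, and its consequence is modest and conditional. If the two factors predict restenosis, the plain log-rank test runs at about 4.4% type I error at 2/2, 4% at 3/2 and 3% at 4/3. At the planned effect it gives up about 0 to 1 point of power for moderate factors, 1.5 to 2 points at 3/2 and 3 points at 4/3. With a smaller effect (HR 0.45) the loss is about 3 to 4 points at 3/2, and reached 5 in one setting at 4/2. All of these figures rest on assumed hazard ratios and prevalences. This is an efficiency improvement that costs almost nothing; it corrects no invalid test.

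**What to change.** Before unblinding, state that the primary test is a log-rank test stratified by occlusion versus stenosis and endovascular versus hybrid procedure, using the values entered at randomisation, or a Cox score test adjusted for both. Keep the plain log-rank as a supportive analysis and use the same stratified test for reocclusion. If a hazard ratio is reported, take it from the matching stratified or adjusted Cox model. Adjusting the t-test and chi-squared endpoints is optional.

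This takes one or two sentences. Both factors are already held in the randomisation system, and the sample size does not change. Fixing the choice in advance also prevents a later selection between adjusted and unadjusted results. The only statistical cost is a loss of under about 1 point of power if the factors turn out not to be prognostic or some cells are sparse.
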